### Settings

The trial will be conducted in Cali, the third largest city of Colombia. The study will be carried out in six public health care institutions, which offer prenatal care in the first level of complexity to people living in the lowest socioeconomic stratum of the population. These institutions are located in the southwest area from Cali (*Red de Salud Ladera*) and provide services mainly for the government-subsidized population in the Colombian healthcare system. The Ethics Committees of Universidad del Valle and Red de Salud Ladera (Resolution-017/08-UV and SCAH/0408-A/08) approved the trial. All participants will provide written informed consent before entering the study.

### Outcome variables

1. The primary outcome is the change of endothelium-dependent brachial artery flow-mediated dilatation (FMD) after three months of regular aerobic exercise. [Time Frame: Baseline and 32 to 36 weeks of gestation].

2. The secondary outcome is the concentration of F2-isoprostanes in umbilical cord blood of newborn [Time Frame: Delivery].

### Analytic plan

All pregnant women studied will be analyzed according to original group allocation and all changes in outcome variables will be attributed to the assigned treatment. An exploratory analysis will be performed to determine frequency, range, variability, and distribution type for each variable in order to use the most appropriated statistical test when comparisons will be necessary. Subsequently, a descriptive analysis of the socio-demographic characteristics, gestational variables, and baseline measures (x_0_) will be performed for each comparison group. These analyses permit to assess the primary analysis of the data and will be undertaken using the principle of intention-to-treat (ITT). The ITT analysis for this study will include all participants, including those who are not fully compliant and those with missing outcome data. While we plan to implement procedures to minimize loss to follow-up and patient withdrawal, we expect to observe some attrition. We plan to employ multiple imputations to handle missing data in the analysis. Multiple imputations, compared to other case deletion strategies, can provide valid inferences with less restrictive assumptions surrounding the mechanism for missing data [21-23].

Due to that this is an experimental design with two measures of the maternal outcome variable, the first at baseline x_0 _(t_0 _= 16-20 gestational weeks) and the second after interventions x_1 _(t_1 _= 32-36 gestational weeks) in four study groups, a comparative analysis between these measures to establish differences will be executed. In order to perform these comparisons one way ANOVA [24] or Kruskal-Wallis [25] tests will be applied, if appropriated. Subsequently, a multivariate analysis will be carried out and the autocorrelation between repeated measures will be taking in to account. We will use longitudinal analysis methods such as GEE in order to control the differences among measures at baseline and to incorporate incomplete observations into this analysis [26].

In order to evaluate the effects of maternal regular physical exercise and micronutrients supplementation on newborn's oxidative stress (concentration of F_2_-Isoprostanes in umbilical cord blood), a comparative analysis will be executed to establish if the effects are different among study groups using analysis of covariance (ANCOVA), a form of general linear model [26]. We will include the baseline measure as a covariate in the model and pre-specified potential confounding factors: maternal age, previous physical exercise level, tobacco or alcohol consumption, differences in diet report and pregnancy complications such as hypertension and diabetes [26]. These will be included regardless of whether baseline imbalance exists. This approach has been chosen because confounder selection strategies that are based on collected data can result in models with poor statistical properties [26]. This will adjust appropriately for any baseline imbalance and will provide the most powerful analysis. Adjusted estimates of intervention effect from this model will be reported as the primary analysis in the trial publication.

Finally, we will investigate if there is an interaction between the two interventions for the primary outcome at 32 gestational weeks (regular physical exercise) or until the birth (micronutrients supplementation). For these analyses we will include appropriate interaction terms in the models [26]. The trial is not powered to detect these interactions and is likely to have poor precision for the interaction terms. We plan to report regression coefficients for the interaction terms and their 95% confidence intervals.

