### Hypothesis

Supplementation with micronutrients or regular aerobic exercise improves endothelial function in the mother and reduces oxidative stress in newborn.

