## Methods/Design

### Study Design

This is a single blind, randomized controlled 2 × 2 factorial trial designed to evaluate the effectiveness of micronutrients supplementation and regular aerobic exercise during pregnancy. This design provides the advantage of assessing the independent and cumulative effects of the interventions in nulliparous pregnant women.

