### Sample size

Measurement of endothelial function (FMD), validated in several population studies was selected as the critical variable to calculate the sample size. Sample size was conservatively calculated to detect all six pairwise difference between treatment groups with a Bonferroni adjustment for an overall 0.05 type I error (0.05/6 = 0.0083) [20]. A sample size of 320 subjects or 80 per treatment group was estimated. The sample size was calculated assuming a specific difference between the groups of 4.3% in the FMD after 3 months of treatment with 11 of maximum standard deviation. It was accepted a type I error of 0.05, a power of 80%, and it was adjusted by 20% [20].

Eligible women for the present study and those interested in participating will be invited to a pre-test that includes an interview (Visit A) and further assessments that will be performed at the Red de Salud Ladera (Hospital Cañaveralejo, Centro de Salud Meléndez, Centro de Salud Siloé, Hospital Universitario del Valle) and at the Laboratory of Biochemistry of the Universidad of Valle, Cali-Colombia. The first visit will take place between weeks 12 and 20 (Visit B), the second at week 32 and 36 (Visit C) and the last one, after delivery (Visit D).

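### The plan names a four-group one-way test for FMD and nowhere states the exercise or micronutrient contrast that its 2 x 2 factorial hypothesis calls for

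*Protocol article*

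**What the plan says.** **Question posed.** The Hypothesis section of the protocol is worded by intervention: "Supplementation with micronutrients or regular aerobic exercise improves endothelial function in the mother and reduces oxidative stress in newborn". Study Design presents a 2 x 2 factorial and gives its benefit: "This design provides the advantage of assessing the independent and cumulative effects of the interventions in nulliparous pregnant women".

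**FMD analysis.** Outcome variables makes change in FMD from baseline to 32-36 weeks the primary outcome. The Analytic plan describes two measurements in four groups and continues: "In order to perform these comparisons one way ANOVA [24] or Kruskal-Wallis [25] tests will be applied, if appropriated". A multivariate step follows, with GEE as the example, to deal with baseline differences and incomplete observations. Its treatment terms are not given.

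**Newborn outcome and the primary label.** The next paragraph of the Analytic plan describes an ANCOVA for cord-blood F2-isoprostanes, the secondary outcome. It closes by saying that the adjusted estimates from this model will be reported as the trial's primary analysis.

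**Interaction.** The plan will look for an "interaction between the two interventions for the primary outcome at 32 gestational weeks (regular physical exercise) or until the birth (micronutrients supplementation"). It concedes that the trial is not powered for this, and will report coefficients with 95% confidence intervals.

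**Sizing.** The Sample size section states: "Sample size was conservatively calculated to detect all six pairwise difference between treatment groups". It splits the 0.05 error rate equally over the six tests by Bonferroni, which leaves 0.0083 for each.

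**The concern.** A one-way test over four groups has three degrees of freedom and one null hypothesis: all four means are equal. Rejecting it says that some group differs. It does not say whether exercise works or whether micronutrients work, and it estimates neither effect. Kruskal-Wallis yields no factor effect or interaction estimate at all. The pairwise comparisons behind the sample size each use only half of the women.

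The contrast that answers a factor-level question (160 women with the intervention against 160 without) is not written down for FMD anywhere. With the primary label attached to a model for the other outcome, a reader cannot tell which FMD estimate will carry the trial's conclusion. The omnibus test, a pairwise test, a GEE coefficient or an interaction model could each be put forward after the data are seen.

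The interaction sentence adds a smaller defect. An interaction between two factors is one term for one outcome at one time, so it cannot be dated to 32 weeks for one factor and to birth for the other.

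**Working it through.** **Inputs.** From Sample size: difference d = 4.3 FMD points, SD s = 11, 80 women per group (320 in total), pairwise alpha 0.05/6 = 0.0083, power 80%, 20% adjustment. Assumed because the text does not say: two-sided tests, the 20% is loss to follow-up (80 becomes 64 per group), and SD 11 applies to the analysed FMD measure equally in all groups.

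**The plan's own figure.** Per group, n = 2(s/d)²(z₁₋α/₂ + z₀.₈)² = 2 × 6.544 × (2.638 + 0.842)² ≈ 158.5, so 159 per group before the 20% adjustment. The stated 80 is not reproduced. That is a separate point, but it bears on which comparisons 320 women can support.

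**Power with one active factor and no interaction.** Cell means are (0, 0, d, d), with n per cell. All powers come from the noncentral F distribution; for the pairwise test this is the two-sample t-test.

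- Omnibus ANOVA, 3 df: λ = n Σ(mean − grand mean)²/s² = n d²/s².
- Main effect, 1 df, 2n against 2n: the same λ = n d²/s², spent on one degree of freedom.
- One pairwise test, n against n: λ = n d²/(2s²).

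| Test | λ, n = 80 | Power | λ, n = 64 | Power |
|---|---|---|---|---|
| Omnibus, alpha 0.05 | 12.22 | 84.3% | 9.78 | 74.3% |
| Pairwise, alpha 0.0083 | 6.11 | 42.3% | 4.89 | 32.4% |
| Main effect, alpha 0.05 | 12.22 | 93.6% | 9.78 | 87.6% |
| Main effect, alpha 0.025 | 12.22 | 89.3% | 9.78 | 80.8% |

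The last row is the fairer comparator where two factors share an overall 0.05.

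**Both factors active and additive.** Cell means are (0, d, d, 2d). The omnibus test has 99.2% power at n = 80 but does not say which factor acts. Each main-effect test keeps the power in the table.

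**Strongly sub-additive.** All three active cells are d above control: (0, d, d, d). For the omnibus test λ = n × 0.75 d²/s² = 9.17, giving 71.4%. The averaged main effect is d/2 = 2.15, so λ = n(d/2)²/s² = 3.06, giving 41.4% at 0.05 and about 31% at 0.025. The ranking reverses.

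**Sample size on main effects.** With 2(s/d)²(z₁₋α/₂ + z₀.₈)² women per level of a factor:

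- alpha 0.05: 103 per level, 206 in total; 206/0.8 = 257.5, so 258 with 20% loss.
- alpha 0.025: 125 per level, 250 in total; 250/0.8 = 312.5, so 313 with 20% loss.

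On these inputs, 320 women support two main effects at 0.025 each. They do not support six pairwise tests at 0.0083.

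**Interaction timing.** Outcome variables and the visit schedule (Baseline assessments and active follow-up) place FMD at Visits B and C only. The items listed for Visit D, after delivery, include F2-isoprostanes but not FMD. An FMD interaction at birth therefore has no data behind it.

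**The case against.** The strongest reply is that the one-way test is only a first step. The plan does not call it primary, a GEE follows, and interaction terms with regression coefficients normally presuppose a model containing both factors. An article may leave the GEE's terms to a fuller document. This stands in part: a reader might infer that the plan as a whole cannot test its hypothesis, and the text does not show that. What remains is that the article does name tests, that the ones it names do not match its question, and that an interaction coefficient is not a main effect.

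A reader might also infer that the factorial was chosen for the power of its main effects. The protocol does not say so. Study Design speaks of independent and cumulative effects, and Sample size deliberately works from pairwise differences. A four-group analysis is consistent with that sizing, the hypothesis can be read as each intervention against control, and cell comparisons stay interpretable under interaction. Margins or cells is partly a choice of estimand, but the plan has to make it.

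A third inference, that the six pairwise tests would inflate the family-wise error rate, fails because Sample size specifies Bonferroni.

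Finally, the power gain depends on little interaction. The Background says both interventions are thought to increase nitric oxide synthesis, so overlapping effects are plausible. This stands and must be disclosed.

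On timing, the parentheses in the interaction sentence may be meant as how long each intervention runs. If so, the repair is to wording, but the sentence still needs it.

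**Conclusion.** The concern holds for what the protocol writes down: the only fully named between-group test for FMD ignores the factorial structure, no factor-level FMD contrast is stated, the primary label sits with the secondary outcome's model, and part of the FMD interaction is dated to a visit without FMD.

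In size, under the protocol's own difference and SD, a main-effect test at 0.025 gains about 5 percentage points over the omnibus test (89% against 84%; 81% against 74% after 20% loss). It has more than twice the power of a Bonferroni pairwise test (42%; 32% after loss). The larger benefit is interpretive: it answers the question asked.

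This rests on two-sided tests, a common SD of 11 on the analysed scale, equal allocation and little interaction. With all three active groups equal, the omnibus test is the stronger one (71% against 41%).

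**What to change.** 1. Name as primary a linear model for FMD at Visit C with terms for exercise, micronutrients and baseline FMD. If GEE is kept, give it the same factor terms. Attach the primary label to this model and describe the isoprostane ANCOVA as the analysis of the secondary outcome.
2. Report both main effects with 95% confidence intervals at a stated alpha, for example 0.025 per factor.
3. Fit one exercise x micronutrient term for FMD at Visit C and one for isoprostanes at delivery. Remove the reference to birth for FMD.
4. Show cell means and simple effects, and say that main effects average over the other factor and lose power if the effects overlap. Keep the Bonferroni-adjusted pairwise comparisons as secondary.
5. Restate the sample size on the two main-effect contrasts and their alpha. On the stated inputs this needs 313 women with 20% loss at 0.025 each, within the planned 320.

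The cost is more than a change of test name, because the alpha and the sizing rationale must be rewritten together. It needs no extra women, visits or measurements.

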### Baseline assessments and active follow-up

**- Visit B**: measurements of blood pressure, anthropometric parameters, FMD, functional capacity (VO_2Max_), and electrocardiogram. During this visit, the participants will be randomized to one of the four intervention groups. For this purpose, a randomization system using maximum blocks of 10 will be used.

**- Visit C**: within 32 and 36 week period of gestation, measurements described above are repeated.

**- Visit D**: the following pregnancy outcomes will be recorded at postpartum: pregnancy duration, blood pressure, characteristics of delivery (route and duration of delivery, and postpartum haemorrhage), newborn outcomes (gestational age at birth, Apgar score, weight, height, head circumference, and abdominal circumference). With these measures, the following variables will be calculated: weight/height^3^, head circumference/birth weight, and weight/height [27]. In umbilical cord blood, measurements of the following outcomes will be obtained: oxidative stress biomarker (F_2_-isoprostanes). In addition, the number of prenatal controls and information regarding pregnancy complications will be registered.

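### No single primary analysis is fixed for FMD, and the baseline-adjusted model labelled primary is written for cord-blood F2-isoprostanes, which have no baseline

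*Protocol article*

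**What the plan says.** All references are to the protocol article.

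- **Outcome variables:** "The primary outcome is the change of endothelium-dependent brachial artery flow-mediated dilatation (FMD) after three months of regular aerobic exercise". The secondary outcome, cord-blood F2-isoprostanes, has delivery as its only time point.
- **Baseline assessments and active follow-up:** Visit B includes "measurements of blood pressure, anthropometric parameters, FMD, functional capacity (VO_2Max_), and electrocardiogram", and Visit C repeats these measurements. Every randomised woman should therefore have a baseline FMD.
- **Analytic plan, FMD:** the plan notes that "this is an experimental design with two measures of the maternal outcome variable". An exploratory look at the data establishes the "distribution type for each variable in order to use the most appropriated statistical test when comparisons will be necessary". For the four-group comparison, "In order to perform these comparisons one way ANOVA [24] or Kruskal-Wallis [25] tests will be applied, if appropriated". A multivariate step follows: "We will use longitudinal analysis methods such as GEE in order to control the differences among measures at baseline and to incorporate incomplete observations".
- **Analytic plan, missing data:** "We plan to employ multiple imputations to handle missing data in the analysis". The justification offered compares imputation with case deletion.
- **Analytic plan, F2-isoprostanes:** the groups are compared by ANCOVA with the baseline measure and a list of prespecified confounders as covariates. Of this approach the plan says "This will adjust appropriately for any baseline imbalance and will provide the most powerful analysis". The adjusted estimates from this model are to be published as the primary analysis.

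**The concern.** There are three problems with the FMD analysis.

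1. **No designation.** FMD has a first-line test and a later model, and neither is called primary. The only model given that label belongs to the secondary outcome and asks for a baseline value that outcome does not have.
2. **Selection from the data.** The first-line test depends on the observed distribution. The same plan rejects data-driven selection of confounders because of its poor statistical properties, yet lets the data choose the test for the primary outcome.
3. **Unused information.** The first-line test leaves out a baseline already collected on the same scale. Whether the later GEE recovers that information depends on a specification the article does not give.

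At stake are precision on the primary outcome, an estimate that cannot be steered by the choice of method, and a clear basis for handling dropout. An analysis plan that followed the article literally would inherit the misassignment.

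**Working it through.** **Inputs**
- From the Sample size section: difference 4.3, SD 11, alpha 0.05/6 = 0.0083 per pairwise comparison, power 80%, 80 women per group. Two-sided testing is assumed.
- Not in the document: rho, the correlation between baseline and follow-up FMD. It is set to 0.3, 0.5 and 0.7.
- Not stated: whether SD 11 refers to follow-up FMD or to change. Both readings are shown.

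**The plan's own figure**

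n per group = 2 × (2.638 + 0.842)² × 11² / 4.3² = 159 before any inflation. The stated 80 per group is not reproduced. That is a separate matter and does not decide this point; these inputs are used only to give the precision argument a scale.

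**Variance of the treatment comparison, in units of the follow-up variance (equal variances at both visits)**
- Follow-up-only ANOVA: 1
- Change-score ANOVA, or GEE group-by-time with free baseline means: 2(1 − rho)
- ANCOVA: 1 − rho²

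Change relative to ANCOVA is 2(1 − rho)/(1 − rho²) = 2/(1 + rho). Follow-up-only relative to ANCOVA is 1/(1 − rho²).

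| rho | Change | ANCOVA | Excess variance, change | Excess variance, follow-up-only |
|---|---|---|---|---|
| 0.3 | 1.40 | 0.91 | 54% | 10% |
| 0.5 | 1.00 | 0.75 | 33% | 33% |
| 0.7 | 0.60 | 0.51 | 18% | 96% |

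**On the trial's scale**
- *SD 11 is the follow-up SD.* With 80 per group at alpha 0.05/6, power for change versus ANCOVA is 29% vs 48%, 43% vs 59% and 71% vs 80% at the three values of rho. Follow-up-only ANOVA has 43% throughout.
- *SD 11 is the SD of change.* The change score needs 159 per group at every rho. ANCOVA needs (1 + rho)/2 times the unrounded figure: 104, 119 and 135.

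**Does GEE lose precision?** A simulation used 160 vs 160 women, difference 4.3, SD 11, complete data and 1,500 runs. Standard errors at rho 0.3, 0.5 and 0.7 were:
- GEE with free baseline means: 1.43, 1.26, 0.94, the same as the change score.
- GEE with a common baseline mean: 1.15, 1.09, 0.88.
- ANCOVA: 1.15, 1.09, 0.88.

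The answer therefore depends on the form of GEE, which the article does not give.

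**Dropout.** With 20% missing completely at random, all methods were unbiased. A second scenario had about 22% dropout driven by baseline FMD, in opposite directions in the two arms. Bias against the true 4.3 was then:
- GEE on incomplete data, independence working correlation: −1.4, −2.4, −3.3.
- GEE on incomplete data, exchangeable working correlation: about −0.2 to −0.3.
- ANCOVA on observed pairs: about 0.

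GEE on suitably imputed data is valid under missing at random. The open question is which dataset GEE uses. Its stated purpose of taking in incomplete observations suggests unimputed data, while the imputation sentence suggests the opposite.

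**The case against.** A reader might infer more than the text supports in four places.

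- **That the primary FMD analysis is unadjusted.** The ANOVA/Kruskal-Wallis step has no baseline term, but GEE is stated to control baseline differences, and neither step is named primary.
- **That GEE is less precise than ANCOVA.** This holds only for the free-baseline group-by-time form. The stated aim of controlling baseline differences fits the harmless forms at least as well.
- **That the plan contradicts itself on missing-data assumptions.** The claim of weaker assumptions is made for imputation against case deletion. The plan states no missingness assumption for GEE.
- **That Kruskal-Wallis cannot be combined with multiple imputation.** Its approximately chi-square statistics can be combined. The real drawback is that it gives no effect estimate.

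It is also fair to say that working correlation and model form are usually left to an analysis plan, which is not shown. The ANCOVA paragraph may even have been meant for FMD and misplaced. The large GEE bias comes from one deliberately adverse dropout scenario with an independence working correlation.

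Those objections stand. They do not touch what the article itself states: the first-line test is chosen from the observed distribution, no FMD analysis is designated, and the baseline-adjusted primary model is assigned to an outcome measured only at delivery. If the paragraph was misplaced, the document still has to say so.

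**Conclusion.** The point holds as one of designation and misassignment, with a precision gain available at almost no cost. For any rho strictly between 0 and 1, ANCOVA is more precise than change-score ANOVA, follow-up-only ANOVA and free-baseline GEE. The excess variance is 18% to 54% for the change score and 10% to 96% for follow-up-only ANOVA over rho 0.3 to 0.7. These figures rest on an assumed rho and equal variances at the two visits; the power figures also rest on reading SD 11 as the follow-up SD. The documents do not show that the eventual GEE will lose precision or be biased, only that the article leaves this open. The change should be made, but nothing here invalidates the design.

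**What to change.** 1. Name one primary FMD analysis: a linear model (ANCOVA) of Visit C FMD% on the exercise and micronutrient factors and baseline FMD%. Obtain the interaction, or the six pairwise contrasts of the Sample size section, from the same model, so that the four-group comparison is kept. The primary outcome can still be described as change: once baseline is a covariate, modelling follow-up or change gives the same treatment estimates.
2. Fit it in each multiply imputed dataset and pool by Rubin's rules. Use robust standard errors, so that non-normality does not force a choice of test after the data are seen.
3. Make ANOVA/Kruskal-Wallis and GEE sensitivity analyses. For GEE, state how baseline enters and whether imputed data are used.
4. Remove the baseline-measure and primary-analysis wording from the F2-isoprostane model, and keep its prespecified covariates.

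The cost is analysis-plan wording and slightly more programming. No new measurements or participants are needed.

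### The ANCOVA for cord-blood F2-isoprostanes adjusts for a baseline value that is never measured, and this secondary-outcome model carries the primary-analysis label while no FMD model does

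*Protocol article*

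**What the plan says.** The section Outcome variables fixes the order of the endpoints. For the first: "The primary outcome is the change of endothelium-dependent brachial artery flow-mediated dilatation (FMD) after three months of regular aerobic exercise", assessed at baseline and at 32 to 36 weeks of gestation. For the second: "The secondary outcome is the concentration of F2-isoprostanes in umbilical cord blood of newborn [Time Frame: Delivery". The Sample size section uses FMD as the variable that sizes the trial.

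The Analytic plan treats the two outcomes separately.

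- **FMD.** The plan describes an "experimental design with two measures of the maternal outcome variable", with values x0 and x1. It proposes one-way ANOVA or Kruskal-Wallis, followed by a further step: "We will use longitudinal analysis methods such as GEE in order to control the differences among measures at baseline".
- **F2-isoprostanes.** A new paragraph opens: "In order to evaluate the effects of maternal regular physical exercise and micronutrients supplementation on newborn's oxidative stress". It names ANCOVA as the method and continues: "We will include the baseline measure as a covariate in the model". It adds a list of prespecified confounders and says that the approach deals with baseline imbalance and gives the greatest power. It ends: "Adjusted estimates of intervention effect from this model will be reported as the primary analysis in the trial publication".

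**The concern.** Two things in the isoprostane paragraph conflict with the rest of the article.

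First, a baseline-adjusted ANCOVA needs the outcome, or a close proxy for it, measured before randomisation. A newborn's cord blood has no such value. If the mother's isoprostanes are not measured at entry either, the covariate has no source in the study's own schedule.

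Second, the only model in that paragraph is the isoprostane ANCOVA, so the label of primary analysis falls on the secondary outcome. The primary outcome has several candidate analyses and none is designated. At stake is which FMD estimate carries the trial's main conclusion, and whether the isoprostane analysis can claim the precision that the text promises.

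**Working it through.** The point depends on no figure in the article. The check is to trace where each outcome is measured and compare that with what each model requires.

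**Step 1: is there a baseline isoprostane value?**

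| Section | What it schedules |
|---|---|
| Outcome variables | F2-isoprostanes: cord blood, at delivery only |
| Baseline assessments and active follow-up, Visit B | Blood pressure, anthropometry, FMD, VO2max, electrocardiogram; no isoprostanes |
| Same section, Visit C | Repeats the Visit B measurements |
| Same section, Visit D | Isoprostanes in cord blood |
| Biochemical markers | Isoprostanes assayed in cord blood; other laboratory tests are mentioned, but no maternal isoprostane sample |
| Analytic plan | Two measurements (x0, x1) for the maternal outcome only |

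No row supplies a pre-randomisation isoprostane value, maternal or neonatal. The covariate is absent for all 320 planned women.

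**Step 2: which model is labelled primary?**

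| Outcome | Rank in Outcome variables | Methods in Analytic plan | Called primary analysis? |
|---|---|---|---|
| Change in FMD | Primary; sizes the trial | ANOVA or Kruskal-Wallis, then GEE | No method is |
| Cord-blood F2-isoprostanes | Secondary | ANCOVA with a baseline covariate | Yes, by the paragraph's last sentence |

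The rank and the label point to different outcomes. The paragraph's rationale (a baseline covariate, imbalance, power) fits FMD, which has a baseline value, and does not fit isoprostanes, which have none.

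**Step 3: what baseline adjustment can offer where it is possible.** In a linear model, with correlation rho between baseline and follow-up, the residual variance is (1 - rho²) times the follow-up variance, so the reduction is rho². The article gives no correlation, so rho is assumed over a range:

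- rho = 0.3: residual 1 - 0.09 = 0.91, reduction 9%
- rho = 0.5: residual 1 - 0.25 = 0.75, reduction 25%
- rho = 0.7: residual 1 - 0.49 = 0.51, reduction 49%

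These figures apply to FMD. For isoprostanes there is no baseline value of the outcome, so this gain is not available.

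**The case against.** **The isoprostane model can still be fitted.** This stands. Only one term lacks data. The group terms and the listed confounders remain, and the model runs once the baseline term is dropped. A reader might infer that the secondary analysis is impossible, but the article supports only the narrower statement that it cannot be fitted as written.

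**FMD is adjusted for baseline.** This largely stands. A reader might infer that the primary outcome gets only an unadjusted comparison. ANOVA or Kruskal-Wallis is the first step, but the GEE that follows is meant to control baseline differences. The variance reductions above are therefore not a loss that the plan is shown to incur.

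**The endpoint hierarchy is clear.** This stands. A reader might infer that the team is free to headline isoprostanes or FMD after seeing the results. The Outcome variables section ranks FMD first and the Sample size section relies on it. The paragraph on interactions refers to the primary outcome at 32 weeks, which fits FMD, although it also mentions birth. What is open is the choice of model, not of endpoint.

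**Softer readings of the wording.** The baseline measure might mean baseline FMD, since the Analytic plan uses x0 for baseline measures generally. The article does not say so, and baseline FMD would not support the stated imbalance and power argument for a different outcome in a different person. The primary-analysis sentence might mean only that adjusted estimates are preferred to unadjusted ones. That would leave the missing covariate in place and still give FMD no designated model.

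**A separate analysis plan may settle it.** It may, but this is not a detail left out. The article itself names a covariate that its schedule cannot supply and itself assigns the primary label.

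**Conclusion.** The point holds on two counts. The isoprostane ANCOVA calls for a baseline value that is available for none of the 320 women, so the imbalance and power rationale does not apply to that outcome. The label of primary analysis is attached to a secondary-outcome model, while the primary outcome has two stages of analysis and no designated model.

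The consequence is limited. The endpoint ranking is not in doubt, the secondary model works without the missing term, and baseline control for FMD is intended. What remains open is which FMD estimate is the trial's main result. The text should settle that before analysis, because ANOVA, Kruskal-Wallis and GEE need not agree.

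Both counts rest on the article's own measurement schedule and need no outside figure. The reductions of 9%, 25% and 49% are illustrations that rest on assumed correlations and a linear relation between baseline and follow-up FMD.

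**What to change.** 1. In the F2-isoprostane model, delete the baseline measure and the imbalance and power rationale tied to it, and label the model as the secondary-outcome analysis. This point does not require any other change to the confounder list.
2. Attach the primary-analysis sentence to one named, baseline-adjusted model for FMD at 32-36 weeks. One option is an ANCOVA with exercise and micronutrient terms and baseline FMD as covariate. With baseline as covariate, modelling follow-up or change gives the same intervention estimate, so this agrees with the outcome being defined as a change. The planned longitudinal model would also serve, if its specification states how it adjusts for baseline. The contradiction requires that one model be named, not that ANCOVA be preferred.
3. Label the ANOVA or Kruskal-Wallis comparison, and whichever FMD model is not chosen, as supportive.

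The main cost is rewording the isoprostane paragraph; the labels in items 2 and 3 can be stated there. No data collection, visits or participants are affected.
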